## Abstract

**Background:**

Trauma within Native American communities compromises parents’ parenting capacity; thus, increasing childrens’ risk for substance use and suicide over the lifespan. The objective of this manuscript is to describe the Wakȟáŋyeža (Little Holy One) intervention and evaluation protocol, that is designed to break cycles of intergenerational trauma, suicide, and substance use among Fort Peck Assiniboine and Sioux parents and their children.

**Methods:**

A randomized controlled trial with an embedded single-case experimental design will be used to determine effectiveness of the modular prevention intervention on parent-child outcomes and the added impact of unique cultural lesson-components. Participants include 1) Fort Peck Assiniboine and Sioux parents who have had adverse childhood experiences, and 2) their children (3–5 years). Parent-child dyads are randomized (1:1) to Little Holy One or a control group that consists of 12 lessons taught by Indigenous community health workers. Lessons were developed from elements of 1) the *Common Elements Treatment Approach* and *Family Spirit,* both evidence-based interventions, and 2) newly created cultural (intervention) and nutrition (control group only) lessons. Primary outcomes are parent (primary caregiver) trauma symptoms and stress. Secondary outcomes include: Parent depression symptoms, parenting practices, parental control, family routines, substance use, historical loss, communal mastery, tribal identity, historical trauma. Child outcomes include, externalizing and internalizing behavior and school attendance. Primary analysis will follow an intent-to-treat approach, and secondary analysis will include examination of change trajectories to determine impact of cultural lessons and exploration of overall effect moderation by age and gender of child and type of caregiver (e.g., parent, grandparent).

**Discussion:**

Many Native American parents have endured adverse childhood experiences and traumas that can negatively impact capacity for positive parenting. Study results will provide insights about the potential of a culturally-based intervention to reduce parental distress – an upstream approach to reducing risk for childrens’ later substance misuse and suicidality. Intervention design features, including use of community health workers, cultural grounding, and administration in Head Start settings lend potential for feasibility, acceptability, sustainability, and scalability.

**Trial registration:**

ClinicalTrials.gov: NCT04201184. Registered 11 December 2019.

## Introduction

### Background and rationale

There is strong evidence that negative parenting experiences in early childhood are associated with later adolescent and young adult substance use and suicide [1, 2]. The earliest effects of ineffective parenting can be observed in early childhood (0–5 years old), expressed as externalizing and internalizing behaviors, such as aggression and social withdrawal [3–5]. Externalizing and internalizing behaviors in early childhood predicts poor school performance in the middle years, and drug use, anti-social, delinquent, and aggressive behavior, and risk of suicide in middle and late adolescence [4, 6–9]. Early parent behaviors most associated with externalizing behaviors in early childhood include coercive interactions, poor monitoring, and harsh, unresponsive, or rejecting parenting [4, 10, 11]. Parenting styles that have been linked to internalizing disorders include negative criticism, hostility, over-control, and abuse or neglect [5]. Parenting factors associated with childrens’ future substance use and suicide risk include parental stress, alcohol and drug use, parent-child attachment, multigenerational adversity, and poor monitoring [9, 10, 12–14]. Past research has shown high numbers of adverse childhood experiences (ACEs) negatively impact parents’ ability to optimally raise their children. Adults who experience ACEs are at increased risk of depression, substance abuse, and antisocial behavior—risk factors for poor child-rearing practices [15, 16]. ACEs in parents have been linked to high parenting stress, poor parent-child attachment, and harmful parenting practices such as corporal punishment during infancy [17–20]. These trends in parents create a cycle of intergenerational ACEs, whereby children of parents who experience ACEs are at higher risk for ACEs themselves and grow up at risk for perpetuating negative parenting practices [2, 21].

Among all United States (U.S.) populations, Native Americans report the highest ACE scores [1, 22, 23] At a population level, ACEs have a strong dose-response impact, with more ACEs contributing to worse lifetime health outcomes, including increased risk for alcoholism, drug abuse, depression, and suicide attempts [19]. This relationship has also been documented in the participating Fort Peck community. Our prior research with *N* = 288 youth ages 15–24 years old found 96% of the sample reported at least one ACE, 3.5 times higher than other populations (26%) [24]. Additionally, two ACEs were reported by 75% of youth, almost twice that of other studies (40%) [1]. After controlling for age, gender, tribal affiliation, and school attendance, each additional ACE increased the odds of PTSD (60%), depression (30%), suicide attempt (36%), and polydrug use (73%) [1, 24]. To break the cycle of ACEs and negative parenting, early parenting interventions that address risk factors for ineffective parenting through direct training are needed [24–27]. Delivering these types of interventions during developmental transition time periods, such as when children are moving from home settings to their first school days, may be particularly impactful [9].

### Objectives

Accordingly, the objective of this trial is to evaluate the Little Holy One intervention’s impact on known family-based risk and protective factors for youth suicide and substance use, starting in early life, through three specific aims. Embedding community-identified strengths of the Fort Peck Assiniboine and Sioux Tribes, the intervention is designed to: 1) reduce parents stress and trauma-related symptoms using culturally adapted components of the *Common Elements Teaching Approach (CETA*), 2) improve parenting skills (monitoring and nurturing), using components of *Family Spirit* that was designed by Native Americans for use with Native American parents and children, and 3) promote positive tribal identity and communal mastery, and address historical and contemporary trauma, factors found to be protective factors for high-risk substance use and suicide within the participating community, by using cultural components that incorporate traditional practices designed by cultural leaders in the community [1, 28–33].

*Aim 1: To evaluate the effectiveness of community health worker delivered Little Holy One on parent and child behavioral and mental health outcomes, using a randomized controlled trial design.* We hypothesize that a) parents in Little Holy One will experience significant decreases in parenting stress and trauma-related symptoms, and significant increases in positive parenting behavior, tribal identity, communal mastery, and b) their children will have lower levels of externalizing and internalizing behavior compared to children in the active control group condition. *Aim 2: To explore the benefit of specific cultural enhancements (promoting tribal identity and communal mastery) of the intervention on parents’ mental health and well-being, by using a single-case experimental design embedded within the randomized controlled trial*. We hypothesize that specific cultural components will increase the impact of Little Holy One by providing immediate and sustained reductions in parental stress after component completion. *Aim 3: Explore how the social network characteristics (*i.e.*, network size, average strength of ties, heterogeneity, density, % same race, % same age, % same gender) of Native American parents are related to both risk for and protection from suicide and opioid use*. Using ego network data, we will extract information about each respondent’s unique network characteristics as correlates of suicide and opioid. *Aim 3a: Examine the impact of the Little Holy One family-based prevention program on the social networks of Native American parents.* We will use pre- and post-intervention data to explore the effect of the intervention on parents’ social networks. *Aim 3b: Determine whether program effects on social networks mediate effects on suicide and opioid among parents*. The effectiveness of behavioral interventions often occur through multiple strategies, the strategies presented in the parent grant remain unchanged, however, we aim to explore the possible efficacy of the Little Holy One program on social networks as levers of change for conferring reduced risk of suicide and opioid use as the group-based nature of the intervention increase social interaction of parents, increases parenting support networks, and is founded in similar values of cultural strengths.

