### Control condition

The active control condition has interventionists that teach nutrition education topics (Table 2**)** in six group sessions of up to 7–8 parent-child dyads per group. Parents learn about healthy food options, where to access healthy foods, are given healthy recipes, and sample easy-to-make healthy foods with their children. The nutrition lessons are approximately 1 hour in length. Control content was selected by the Tribal Advisory Board based on its potential benefit and interest to participating families, with minimal risk for contaminating intervention outcomes.

**Table 2 Tab2:** Lesson schedule for all study participants

Week	Little Holy One Lessons (Intervention)	Nutrition Lessons (Control)
1	**Ą́**ba Wasté / Aŋpétu Wašté (Promoting Tribal Identity)	Racing Towards Healthy Eating
2	Understanding our Emotions	–
3	Azí’įc’iya / Azídya (Promoting Smudging)	Fun with Food Groups!
4	Thinking Positively	–
5	Encouraging Early Learning	Portion Sizes
6	Daily Routines for Caregivers and their Children	–
7	Alcohol and Drug Use	Making Your Plate
8	Monitoring your Child’s Routine	–
9	Strengthening Family and Community (Enhancing Communal Mastery)	Rethink Your Drink!
10	The Power of Our Memories	–
11	Healing Historical Trauma	Savor It: Smell, See, Taste!
12	Skills for Effective Caregiving	–

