### Lesson frequency and duration

Participants in the intervention group will be taught the 12 lessons over a 16-week period in individual sessions with their community health worker—a delivery strategy selected to enhance participant engagement, local acceptability, and sustainability [47, 48]. Lessons will be delivered at a location that works best for the participant, including Head Start locations, community centers, or study office space at a convenient time (i.e., after drop-off or pick-up). Participants in the control group will participate in group or individual lessons on nutrition at a convenient time and place for participants. Both the intervention and control lessons will begin 2 weeks after study enrollment, and baseline assessments and randomizations have been completed. Participants in both conditions will be assessed by blinded evaluators using mobile data collection at baseline, 12 weeks (when intervention ends), and 6-, 12-, 18-, and 24-months follow-up. Figure 2 outlines the overall flow of the study below.

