### Statistical methods

#### Aim 1

The primary effectiveness aim will be assessed on a full intent-to-treat basis. The design incorporates longitudinal measurements that led to a nested data structure. For Aim 1 there are 5 repeated assessments (level-1) nested within children and caregivers (level-2) nested with 4 community health workers (level-3). Given the complexities of nested data, we will use mixed-effects regression models to analyze the data. Mixed-effects regression models are highly flexible and accommodate variability in the number and spacing of assessments within and across participants, continuous and discrete outcome distributions, varied patterns of change over time (e.g., quadratic), and phase-specific change (i.e., discontinuous or piecewise change [79, 81, 82]. To build our outcome models, we will first explore outcome trajectories graphically and descriptively evaluated to determine the best distribution for modeling using “spaghetti plots.” We will then iteratively build our estimation models using the approach described in Singer and Willett [83]. The first model will estimate the proportion of outcome variance at each level; the second model will add growth terms; the third model will add fixed-effect indicators to test for differences in baseline characteristics if necessary [83]. If there are differences in baseline characteristics between the intervention groups, these will be statistically controlled in models that follow. The fourth, and final, model will add the condition indicator (i.e., 0 = WLC, 1 = Little Holy One) and cross-level interaction effects between condition and level-1 terms.

#### Aim 2

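### Aim 3 is justified by group delivery of an intervention that is taught individually, and the Aim 1 model has no term for control session groups

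*Protocol article*

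**What the plan says.** **Intervention format.** The Aim 3 text under Objectives expects an effect on social networks because "the group-based nature of the intervention increase social interaction of parents". Lesson frequency and duration says that intervention participants are "taught the 12 lessons over a 16-week period in individual sessions with their community health worker".

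**Control format.** Control condition describes nutrition teaching "in six group sessions of up to 7–8 parent-child dyads per group". Lesson frequency and duration is looser: "Participants in the control group will participate in group or individual lessons on nutrition".

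**Other reasons for a network effect.** Statistical methods, Aim 3, bases the expected change on the cultural content of the intervention arm. Conceptual model points to relational teachings and to community health workers as means of strengthening ties. Neither reason needs group sessions.

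**Aim 1 model.** Statistical methods sets out repeated assessments within caregivers and children, "nested with 4 community health workers (level-3". The structure is not arm-specific, and no level is given for the control session groups.

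**The concern.** The two statements about intervention format cannot both hold. If the Methods text is followed, the contact among parents that Aim 3 invokes does not occur in the intervention arm, and the only place where it can occur is the control arm.

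Aim 3a compares network change between arms from before the intervention to the first assessment after it. If control parents meet each other repeatedly, a null or negative contrast could reflect the format of the control rather than a lack of effect of the curriculum. Aim 3b, which treats network change as a mediator, inherits that ambiguity. Nothing described in the article separates the two explanations.

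The same feature matters for the primary analysis. Families who share a nutrition group may have correlated outcomes, while individually taught families do not share sessions. A model with only a worker level above the participant cannot tell apart several groups led by the same worker, and a variance estimated from four workers is imprecise. Group correlation that the model does not capture makes the standard error of the arm difference too small.

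**Working it through.** **1. The plan's own figure.** Sample size and power, Aim 1, divides the observations by 1 + (cluster size − 1)ρ.

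- 120 × 5 = 600 observations; 600 × 0.70 = 420 after 30% attrition.
- With cluster size 5 and ρ = 0.3: 420 / (1 + 4 × 0.3) = 420 / 2.2 = 190.9. This reproduces the stated 190.

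The cluster size that reproduces the figure is the five repeated assessments. The article says that ρ also covers nesting within schools, but no session-group size enters the calculation.

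**2. Number of control groups.** 120 dyads at 1:1 give 60 controls. Randomization process and study flow gives 30 controls a year, so about 15 a semester, which fits two groups of 7–8. Over the trial, 60 / 7.5 = 8 groups.

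**3. Effect of leaving out the groups.** The documents give neither an ICC for families in the same nutrition group nor the share of controls taught in groups. Both are assumed here: ICC 0.02, 0.05 and 0.10; share 100% and 50%. A two-sided 5% test is also assumed.

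- Design effect among grouped controls: 1 + (7.5 − 1) × ICC = 1.13, 1.325, 1.65.
- Control-arm design effect D: share × that value + (1 − share).
- Intervention arm: 1. Average over equal arms: A = (1 + D) / 2.
- True standard error relative to the unadjusted one: √A.
- Actual type I error: 2 × [1 − Φ(1.96 / √A)].
- Effective n: 190.9 / A.

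| Share grouped | ICC | D | A | √A | Type I error | Effective n |
|---|---|---|---|---|---|---|
| 100% | 0.02 | 1.13 | 1.065 | 1.032 | 5.8% | 179.2 |
| 100% | 0.05 | 1.325 | 1.1625 | 1.078 | 6.9% | 164.2 |
| 100% | 0.10 | 1.65 | 1.325 | 1.151 | 8.9% | 144.1 |
| 50% | 0.02 | 1.065 | 1.0325 | 1.016 | 5.4% | 184.9 |
| 50% | 0.05 | 1.163 | 1.0813 | 1.040 | 5.9% | 176.6 |
| 50% | 0.10 | 1.325 | 1.1625 | 1.078 | 6.9% | 164.2 |

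**4. What these figures leave out.** They assume groups at near-maximum size and no absorption by the worker level. Attrition of 30% would cut the mean analysed group to about 7.5 × 0.70 = 5.25 families and lower the inflation. In the other direction, the normal approximation ignores the small number of groups.

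**The case against.** - **Control lessons may be individual.** One section allows this, and 7–8 is a maximum. This stands: the share in groups is unknown, so the figures for full grouping are an upper scenario. It is also a second inconsistency for the protocol to settle.
- **The network mechanism is not reversed.** A reader might infer that the design hands the mechanism to the control arm. The documents do not support that. The content-based and relational reasons survive individual delivery, the questionnaire covers only up to 10 of the closest relationships, and six nutrition sessions of about an hour each would have to alter those. One stated reason fails; the direction of effect stays open.
- **Clustering is not ignored outright.** The model has a worker level. The Abstract speaks of a "control group that consists of 12 lessons taught by Indigenous community health workers", which can be read to mean that the same workers teach both arms, while Control condition says only interventionists. If workers do lead control groups, their level may absorb part of the correlation. It still cannot separate groups that share a worker.
- **Modelling detail belongs in an analysis plan.** Fair for degrees of freedom and variance structure, whose absence is not held against the article. The hierarchy, however, is stated, and following it as written leaves the groups out.
- **Aim 3 is exploratory.** True. That limits the weight of the point but does not resolve the contradiction.

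**Conclusion.** The contradiction on intervention format is certain and needs no assumption. As written, the group-contact reason for Aim 3 does not apply to the intervention arm and may apply to the control arm, so delivery format and arm are confounded in the 3a contrast and in 3b mediation. How strongly, and in which direction, the documents do not show.

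For Aim 1, the stated hierarchy understates the standard error to the extent that controls are taught in groups and the worker level does not absorb the correlation. On the assumed ICCs, type I error lies between about 5.4% and 8.9%. This is a conditional illustration, not an estimate.

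A reader might also infer that the sample size fails. It does not on the protocol's own criterion: the lowest effective n shown, 144.1, is above the target of 120. The issue is the validity of the standard errors. The matter should be put right before analysis, but it does not undermine the trial.

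**What to change.** 1. Reconcile Objectives (Aim 3), Control condition, and Lesson frequency and duration on delivery format in both arms. Restate the Aim 3 rationale so that it does not depend on group delivery of the intervention.
2. For each control family, record whether lessons were group or individual and, if group, which group.
3. In Aims 1 and 3a, add a random effect for session group in the control arm only, treating individually taught families as singletons, with small-sample degrees of freedom. Replace the four-worker random effect by a fixed worker effect only if workers serve both arms. The documents do not establish this, and if each worker serves one arm the fixed effect is collinear with arm.
4. Keep the full-network contrast as the main 3a analysis. Excluding ties met through study lessons is at most a sensitivity analysis, because such ties are a consequence of allocation and removing them changes the effect being estimated. That analysis would need one added item in the network questionnaire.

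The cost is revised wording, a format field and a group identifier for control families, an optional questionnaire item, and slightly wider confidence intervals.

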## Methods

### Conceptual model

Our conceptual model (Fig. 1), developed in partnership with our participating communities, drove selection of the three core intervention components: 1) Elements of *CETA* will be applied to reduce parents’ stress and trauma-related symptoms. 2) Elements of *Family Spirit* will be applied to improve parenting. 3) Cultural components will promote tribal-specific protective factors, including positive tribal identity and communal mastery while buffering the effects of historical trauma [27, 31, 34–37]. The curriculum is designed to be strengths-based and holistic, promoting family wellness across mental (cognitive), physical (behavioral), emotional (feelings), and spiritual domains represented as balanced quadrants in the Native American Medicine Wheel. Further, both the relational nature of the cultural teachings and the employment of culturally embedded community health workers to teach the curriculum are intentional design choices aimed at strengthening relational ties between parents and children, families and community health workers, and families and the community. This strategic approach responds to the growing literature about the important role that connectivity plays in prevention of suicide risk among Native Americans [32, 33]. Little Holy One is designed to impact modifiable components of parenting, mental health, and culture to reduce early childhood risk for behavioral health outcomes.

**Fig. 1 Fig1:**
[figure not shown]
Little Holy One conceptual model

### Trial design

This is a randomized controlled trial (RCT) with 1:1 randomization of 120 parent-child dyads to Little Holy One or an active control group. Within the RCT there is an embedded single-case experimental design (SCED) aimed at exploring the added impact of specific cultural components [38].

### Study setting

The study is taking place on the 2-million-acre Fort Peck Reservation. The Fort Peck Reservation was established by treaty in 1888, in rural northeastern Montana, and home to ~ 13,000 Dakota and Nakoda members, 50% of whom are < 18 years [34, 35, 39]. The reservation lies within one of the poorest and least healthy counties in the United States (U.S.) [2, 31]. In 2011, the violent crime rate was five times the state and three times the U.S. rate. Health and safety are the highest priority concerns for the tribal nation [34, 35, 39].

### Participants

Participants are parents and their children ages 3–5 years old, who are enrolled in Fort Peck Head Start (*N* = 120 dyads). Intervention and data collection will be completed in private locations, convenient for participants, including Head Start centers, study offices, and homes in the reservation communities of Poplar and Wolf Point. Head Start is a federal program run through the U.S. Department of Health and Human Services intended to prepare children from low-income families for school [40]. Two of the four Head Start centers on the reservation are participating, as they primarily serve children ages 3–5 years old. The Fort Peck Head Start Program averages about 237 students ages 3–5 years old per year; approximately 80% live below the 100% poverty level, and 40% are from single-parent families. In 2015, the parent age distribution was 12–24 years (16%), 26–35 years (66%), and 35–45 years (18%).

